### Quality assurance and safety

Process flow and quality management of the study will be supervised quarterly by a scientific advisory board in repeated audits with study staff. The scientific advisory board will be involved in all decisions on important protocol modifications (e.g., changes to eligibility criteria, outcomes, analyses), followed by informing the relevant parties (investigators, trial participants, trial registries, journals, regulators).

During the intervention, each GP in the intervention group will be contacted at least twice by telephone to evaluate the progress of the study and to get information about potential harms for the patients regarding the safety parameters. Evidence suggests that serious AEs such as cardiovascular events (myocardial infarction, stroke) or death are not anticipated. Potential minor AEs are hyperglycaemia, elevated blood pressure, and recurrence of symptoms (e.g., dyspnoea, oedema) after stopping medication. The events will be reported to the data and safety monitoring board (DSMB) and relevant regulatory bodies as required, indicating expectedness, seriousness, severity, and causality.

To ensure high data quality, assessors (study nurses) will be trained on standardised patients regarding how to interview the patients and how to use the assessment tools. The personnel of the participating practices will not be involved in the collection of data.

Reliability training and checks will be performed before starting the study with the whole staff involved in interviewing and data collection. The quality assurance consists of procedures for prevention of insufficient data quality, detection of inaccurate or incomplete data, and action to improve data quality. In addition, the centres will regularly receive feedback by quality reports for data quality. External monitoring (e.g., for source data verification) would be desirable but too cost-intensive. As a solution, a random sample of paper crucial structure- and process-related factors will be compared with the data entries in the database.

For supervision of the study concerning the safety parameters and safety rules, a DSMB will be constituted. The DSMB will meet at least every 3 months starting and will evaluate the continuously collected safety parameters in a quarterly safety report. For this panel, at least two clinical and/or pharmacological researchers will be recruited who are not part of the COFRAIL project team or advisory board.

If the hospitalisation rate in the intervention group or in the control group will exceed more than 100% in comparison to the other group, the DSMB will inform the primary investigator. The primary investigator shall be responsible to consider further action to assure the safety of the study patients in consensus with all project partners and the DSMB.

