#### Primary outcome

The primary endpoint of the study is the number of hospitalisations per patient during the observation period of 12 months. This outcome does not include visits to an outpatient clinic or visits to an emergency unit without hospital admission. The hospitalisations will be documented by the participating GPs after 6 and 12 months and by the patients in their event diary. In case of disparity between the number of hospitalisations documented by GPs and patients, the study centre will be requested to validate the information on hospitalisation. If the information cannot be clarified, the higher value will be used for data analysis.

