Weight		X			X		X
Number of falls		X			X		X
Use of emergency services		X			X		X

*Abbreviations: CERAD* Consortium to Establish a Registry for Alzheimer’s Disease, *DBI* Drug Burden Index, *GDS* Geriatric Depression Scale, *NHPP* number of hospitalisations per patient, *PIM* potentially inappropriate medications, *SPIRIT* Standard Protocol Items: Recommendations for Interventional Trials, *TNM* total number of medications

Participant retention and complete follow-up will be promoted via phone calls by the study nurses. For patients who drop out of the study, the following parameters are requested by the GPs: hospitalisations, cardiovascular events (e.g., stroke, myocardial infarction), mortality, and other adverse events (AEs).

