#### Additional safety parameters

The GPs will be requested to document cardiovascular events (e.g., stroke, myocardial infarction) and mortality after 6 months (T_1_) and after 12 months (T_2_). The following safety parameters, if available, will be collected every 3 months by the GPs from the records:
Blood pressure level (mmHg)Heart rate (beats/min)Laboratory results: blood sugar (mg/dl), estimated glomerular filtration rate

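### Harm-eliciting telephone calls go to intervention GPs only, so harms with no scheduled collection in both arms (chiefly symptom recurrence) are ascertained unequally

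*Protocol article*

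**What the plan says.** All references are to the protocol article.

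**Quality assurance and safety** states that "each GP in the intervention group will be contacted at least twice by telephone to evaluate the progress of the study" and, in the same sentence, "to get information about potential harms for the patients regarding the safety parameters". The section does not mention control GPs in this connection. It then lists the adverse events that are thought possible: "Potential minor AEs are hyperglycaemia, elevated blood pressure, and recurrence of symptoms (e.g., dyspnoea, oedema) after stopping medication". Adverse events go to the DSMB with a grading of expectedness, seriousness, severity and causality, and the DSMB reviews a safety report every quarter. The one between-arm rule concerns the hospitalisation rate: the DSMB acts when the rate in one arm exceeds that of the other by more than 100% ("in comparison to the other group").

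Other sections describe safety collection that is not restricted by arm:

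- **Additional safety parameters:** "The GPs will be requested to document cardiovascular events (e.g., stroke, myocardial infarction) and mortality after 6 months", and again at 12 months. For blood pressure, heart rate and laboratory values: "The following safety parameters, if available, will be collected every 3 months by the GPs from the records".
- **Primary outcome:** "The hospitalisations will be documented by the participating GPs after 6 and 12 months and by the patients in their event diary".
- **Secondary outcomes**, closing paragraph: "For patients who drop out of the study, the following parameters are requested by the GPs". The list that follows covers hospitalisations, cardiovascular events, mortality and other adverse events.

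**Process evaluation** also mentions telephone monitoring of physicians and patients. It names no arm and does not say that harms are asked about. **Study design** states that the trial is open label and that only outcome assessors are blinded.

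**The concern.** How many harms are recorded depends partly on how hard one looks. Here one arm's GPs are asked about harms by telephone at least twice, and the other arm's GPs are not. The GPs who report know their allocation. If events found through the calls are counted next to control-arm events that nobody asked about, the intervention arm will show more harm even when the true risks are equal.

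This matters because the intervention encourages the withdrawal of medicines, and the trial is presented as a test of patient safety. An apparent excess of recurrent symptoms could mislead the DSMB or weaken the case for implementation, when it reflects only the extra questions. The likely direction is against the intervention.

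**Working it through.** **Step 1. Which harms depend on the calls?** Setting the sections side by side:

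| Harm | Collection described | Restricted by arm? |
|---|---|---|
| Deaths, cardiovascular events | GP documentation at 6 and 12 months; also for drop-outs | No |
| Blood pressure, heart rate, blood sugar, kidney function | GP records every 3 months, where available | No |
| Hospitalisations | GP documentation at 6 and 12 months plus patient diary; also for drop-outs | No |
| Other adverse events in drop-outs | Requested from GPs | No |
| Symptom recurrence in patients who stay in the trial | No scheduled collection; the telephone calls are the only harm enquiry described that could reach it | Yes, intervention only |

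Of the three minor events that the article names, hyperglycaemia and elevated blood pressure can be read at least in part from the quarterly values. Symptom recurrence cannot. It is the item most exposed.

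**Step 2. How large could the distortion be?** The article gives no adverse-event rates and no capture rates, so there is no stated figure to reproduce and all values here are assumptions. Let p be the true risk, equal in both arms, and let c_C and c_I be the proportions of events captured in the control and intervention arms.

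Observed risk = p × c, so the apparent ratio = c_I / c_C, whatever p is.

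| c_C | c_I | Apparent ratio |
|---|---|---|
| equal | equal | 1.00 |
| 0.90 | 0.95 | 0.95 / 0.90 = 1.06 |
| 0.70 | 0.90 | 0.90 / 0.70 = 1.29 |
| 0.50 | 0.80 | 0.80 / 0.50 = 1.60 |

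The same model can be written with a recovery fraction r, the share of otherwise missed events that the calls pick up: c_I = c_C + r(1 − c_C). With r = 0.5:

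- c_C = 0.70: 0.70 + 0.5 × 0.30 = 0.85, and 0.85 / 0.70 = 1.21.
- c_C = 0.50: 0.50 + 0.5 × 0.50 = 0.75, and 0.75 / 0.50 = 1.50.

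Both lie inside the range above. The 1.60 is an illustration and not an upper limit, since the ratio grows as c_C falls.

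**Step 3. Could it look statistically convincing?** The article describes no test of adverse events, so this step only gives a sense of scale. The sample-size section supplies the numbers per arm, and its figures reproduce: 253 × (1 + 4 × 0.05) = 253 × 1.2 = 303.6, so 304 per arm and 608 in total; 608 / 0.9 = 675.6, so 676. The effective size per arm is 304 / 1.2 = 253.3, if the intra-cluster correlation assumed for hospitalisations also applied to adverse events.

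With observed risks p_C and p_I, the chance of a nominally significant excess in the intervention arm (two-sided 0.05) is about

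Φ( (p_I − p_C) / √{[p_C(1 − p_C) + p_I(1 − p_I)] / 253.3} − 1.96 ).

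| Capture, control vs intervention | True risk 10%: observed | Chance | True risk 20%: observed | Chance |
|---|---|---|---|---|
| 0.90 vs 0.95 | 9.0% vs 9.5% | 4% | 18% vs 19% | 5% |
| 0.70 vs 0.90 | 7.0% vs 9.0% | 13% | 14% vs 18% | 23% |
| 0.50 vs 0.80 | 5.0% vs 8.0% | 28% | 10% vs 16% | 52% |

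With no distortion this chance would be 2.5%. The effect is negligible when routine capture is already high and material when it is poor.

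**The case against.** The best defence is that most of what matters for safety is collected alike in both arms. Deaths, cardiovascular events, quarterly values and hospitalisations have routes with no restriction by arm. The calls ask about harms in relation to the safety parameters, and these are largely the same items. Adverse events are neither a primary nor a secondary outcome, and no between-arm test of them is described. Telephone contact is a reasonable safeguard in the arm where medicines are being withdrawn. The layout of safety tables is normally left to a statistical analysis plan or DSMB charter, and neither is shown.

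Much of this stands, and it rules out three stronger readings that a reader might infer.

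- *All adverse-event comparisons are biased.* The shared routes contradict this. The calls could prompt fuller reporting of those items too, particularly the quarterly values that are taken only where available, but the article does not show that they do.
- *The DSMB's comparison of the arms is compromised.* The only stated between-arm rule uses hospitalisations, which come from GPs and patient diaries in both arms.
- *The primary endpoint is distorted.* An unresolved disagreement between GP and diary takes the higher value, so fuller GP reporting in one arm could only raise that arm's count. But collecting admissions is not a stated purpose of the calls. The diary is a second source, and any such effect would work against the intervention, so it could not create a false benefit.

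The defence does not remove the core. The restriction of the calls to one arm is stated in the article itself and is not a detail left to another document. The telephone monitoring under Process evaluation might include control practices, but with neither arm nor harm content given it cannot be counted as a matching enquiry. For symptom recurrence in patients who stay in the trial, no common route is described.

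**Conclusion.** The point holds in a limited form. As written, the article creates unequal ascertainment of harms that lack scheduled collection in both arms, chiefly symptom recurrence among patients who remain in the trial. Any between-arm summary that includes call-elicited events would tend to overstate harm in the intervention arm.

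The direction follows from the design, but the size does not. The range of about 1.06 to 1.6 rests wholly on assumed capture rates and should not be read as an estimate. Where capture is equal, as it may be for deaths, the ratio is 1.0. The conclusion assumes that no matching harm enquiry to control GPs exists in the full protocol. It is a point about how safety data are compared, and it changes neither the sample size nor the primary analysis.

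**What to change.** Keep the calls as safety oversight. Add a statement to the protocol, and carry it into the analysis plan and DSMB charter, that:

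1. between-arm safety summaries, including those given to the DSMB, use only items collected by the same form and on the same schedule in both arms; and
2. harms elicited through the calls are listed separately and labelled as intervention-arm information without a control-arm counterpart.

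This costs wording only. The downside is that call-elicited events leave the comparative tables, so recurrent symptoms in patients who stay in the trial would be described for one arm and not compared.

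The alternative is to put the same harm questions to control practices on the same schedule. With an equal split of 136 GPs that is 68 × 2 = 136 further calls at the minimum of two each. It would permit a comparison, but it adds staff work and might cue control GPs to deprescribing, an aim that the recruitment section keeps undisclosed at its information events. It is not needed to resolve the point.

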### Dissemination policy

The results of the study will be published in brief reports on the website of the project and in user-friendly journals for GPs and other health professionals. For scientific dissemination, the study results will be presented at national and international scientific conferences on health care research, general practice, and clinical pharmacology. We will publish the obtained scientific findings of the trial preferably in open-access journals.

## Discussion

This study will provide evidence for a co-operative and patient-centred educational intervention using family conferences to improve patient safety in frail elderly patients with polypharmacy.

To our knowledge, this is the first randomised controlled trial aiming to assess the effects of family conferences on the safety of patients with geriatric frailty and polypharmacy. The intention of this project is to contribute to the complex process of deprescribing that is often characterised by vague fears of legal consequences and unclear responsibilities of the encountered actors. The strength of this study is that it will be conducted in daily clinical practice.

In case of a positive evaluation of our intervention, transfer and implementation to the German health care system could be realised in three steps. First, applicable recommendations for performing regular family conferences in patients with frailty and polypharmacy should be added to future clinical guidelines on management of multimorbidity and polypharmacy. Second, German statutory health insurance might consider paying GPs for conducting family conferences in usual care or within the limits of selective contracts. Third, family conferences may be an eligible part of a future disease management programme on multimorbidity and polypharmacy. As this project is funded by the Innovationsfonds of the German Federal Joint Committee aiming only at projects with a high potential for implementation in the German health care system, there is a realistic chance for it, given a positive outcome of the trial.

## Trial status

Patient recruitment opened on 15 March 2019 and is expected to continue to 31 March 2020. Protocol version number 1.1 (15 February 2020).

## Data Availability

Data cannot be made available, owing to the European Union General Data Protection Regulation. Readers who are interested in study materials (e.g., model consent form) should contact the corresponding author.

## Abbreviations

ADR: Adverse drug reaction
AE: Adverse event
CERAD: Consortium to Establish a Registry for Alzheimer’s Disease
COFRAIL: Family Conferences and Shared Prioritisation to Improve Patient Safety in the Frail Elderly
CRF: Crucial structure- and process-related factors
DBI: Drug Burden Index
DSMB: Data and safety monitoring board
GDS: Geriatric Depression Scale
GP: General practitioner
ICER: Incremental cost-effectiveness ratio
ICUR: Incremental cost-utility ratio
NHPP: Number of hospitalisations per patient
PIM: Potentially inappropriate medications
QALY: Quality-adjusted life-year
TNM: Total number of medications
